### Measures

The study measures described below will be administered online using Qualtrics.

#### Participant Information Form

The study investigators developed this form to collect demographic information including the participant’s age, sex, gender identity, racial/ethnic background, marital status, education, employment status, income levels, and perceptions of their weight and food security. Completing this form should take no more than 10 minutes.

#### Pre-Interaction Questionnaire

This 15-question instrument includes 12 five-point Likert-scale questions adapted from the Psychometric Analysis of the Perceptions of Computerized Therapy Questionnaire-Patient version (PCTQ-P) [113]. The PCTQ-P is a validated measure grounded in the diffusion of innovations theory [114] previously shown to be effective at predicting successful dissemination of evidence-based mental health interventions [115]. The goal of these questions is to assess the participants’ degree of exposure to and perceptions of AI conversational agents in general, including the detection of any presuppositions and biases towards AI, their attitude about AI counselors, preference for AI over human counselors, and belief in the ability of AI counselors to facilitate weight loss. The questions about participants’ attitudes toward AI counselors, preference for AI over human counselors, and beliefs in the ability of AI counselors to facilitate weight loss are also assessed post-interaction. The Pre-Interaction Questionnaire also includes 3 weight loss motivational assessments, in which the participants are asked to rate their confidence, importance, and readiness to change their weight-related lifestyle behaviors using a ruler ranging from 1 to 10, where 1 indicates “not at all” and 10 indicates “very much” [21]. These assessments are repeated in the Post-Interaction and Follow-Up Questionnaires. Completing this questionnaire should take no more than 15 minutes.

#### Post-Interaction Questionnaire

This instrument includes 16 five-point Likert-scale questions adapted from PCTQ-P and the confidence, importance, and readiness rulers assessed in the Pre-Interaction and Follow-Up Questionnaires. Completing this questionnaire should take no more than 15 minutes.

#### Usability Questionnaire

This instrument includes 15 five-point Likert-scale questions from the Telehealth Usability Questionnaire [116], a validated measure that combines the questions from popular traditional computer technology questionnaires, such as the Technology Acceptance Model [117] and the IBM Post-Study System Usability Questionnaire [118]. The Telehealth Usability Questionnaire was adapted for this study to assess perceptions of NAOMI’s usability, such as usefulness, ease of use, reliability, and satisfaction. Completing this questionnaire should take no more than 15 minutes.

#### Consultation and Relational Empathy Measure

The 10-question validated Consultation and Relational Empathy (CARE) measure [119] was adopted by the investigators to assess NAOMI’s empathic skills. Answers are converted to a numeric summary score on a 0-100 scale allowing the investigators to directly compare NAOMI’s empathic skills with those of human or other AI counselors. Completing this measure should take no more than 10 minutes.

#### Follow-Up Questionnaire

This instrument includes the confidence, importance, and readiness rulers assessed in the Pre- and Post-Interaction Questionnaires. Completing this questionnaire should take no more than 5 minutes.

#### Semi-Structured Qualitative Interview

Research staff will use a semi-structured interview guide composed of 13 questions to query participants’ prior experience with other conversational agents or AI counselors and to gather feedback on their interaction with NAOMI, including the usefulness of NAOMI’s advice, quality of its counseling, and suggestions for improving NAOMI. The qualitative interview should take no more than 45 minutes.

### Recruitment

#### Setting

We will recruit participants from the primary care clinics in Detroit, Michigan, and the greater Metropolitan Detroit area that are part of the MetroNet primary care practice-based research network [120]. Developed in 2001 with federal funding, MetroNet is a collaborative effort of the Wayne State University’s Department of Family Medicine and Public Health Sciences, its affiliated family medicine residency programs, and 10 community-based primary care practices serving the diverse population of approximately 50,000 patients from Metropolitan Detroit (≈60% identifying as African American, 30% White, 5% Arab/Chaldean, and 5% Hispanics).

#### Inclusion Criteria and Target Sample Size

To be included in this study, patients must be (1) English-speaking, (2) aged 18 years 0 months to 65 years 0 months, and (3) meet criteria for overweight or obesity (BMI 25.0-39.9) as documented by their treating physician. The exclusion criteria are in line with other similar studies [121]: (1) comorbid conditions that might compromise data integrity or the patient’s ability to autonomously interact with NAOMI (eg, severe autism, schizophrenia, or other psychotic disorders), (2) patients whose elevated weight is secondary to another medical condition (eg, Prader-Willi), and (3) women who are pregnant. Following literature recommendations for sample size in feasibility studies [122,123], we are planning to recruit 50 (12-13 per each of the 4 study cycles to account for possible attrition between the study visit and a follow-up survey) participants to ultimately have 40 participants (10 per cycle), who will have completed both the study visit and a follow-up survey.

#### Procedures

MetroNet primary care clinics will be sent an introductory email describing this study and inviting them to serve as recruitment partners. Emails will be followed up by the study staff, who will make phone calls to assess interest and discuss the project in more detail. Clinics that agree to partner will be asked to identify a staff member to liaise with the study team in the recruitment of study participants from their clinical population. Patients eligible for participation in this study will be identified through a review of the participating clinics’ medical charts either by clinic or authorized study staff and recruited using 2 approaches.

In the first approach, clinicians will briefly introduce the study to eligible patients at the end of their in-person clinic visit. If a patient is interested in learning more about the study, they will either sign a Release of Contact Information Form to be forwarded to the study staff for follow-up or, if study staff are available in the clinic, they will meet with the patient to discuss the study and their interest in participating.

In the second approach, all potentially eligible patients identified via chart review will be mailed a letter of introduction explaining the purpose of the study and offering the opportunity to opt out of further contact. The study staff will follow up with the patients who do not opt out to present the details of the study, assess their interest in participating, and schedule interested patients for their study visit.

### System Versions and Training

We will develop and evaluate NAOMI in 4 stages. To determine the general direction for developing NAOMI, in stages 1 and 2, it will be implemented using an open-source foundation LLM and (1) using few-shot learning based on a prompt with task-specific instructions and examples of key counselor communication behaviors, and (2) using a domain adaptation strategy based on 1555 transcripts of psychotherapy sessions and 205 transcripts of MI sessions gathered in our previously funded studies to fine-tune the LLM with communication patterns and the language of MI counseling. In stages 3 and 4, we will refine the best approach.

### Data Analysis

We will use a combination of statistical, qualitative, and thematic approaches to analyze the data collected during this study.

#### Statistical Analysis

NAOMI’s adherence to the core principles of MI will be assessed using the MITI coding scheme [111], a standard instrument for assessing MI fidelity. Two trained MITI coders (the primary and secondary) will code NAOMI’s utterances in the transcripts of its interactions with the study participants with MITI codes. The primary coder will code all transcripts with the second coder co-coding randomly selected 25% of transcripts to assess interrater agreement using the Krippendorff α statistic [124]. The quantitative assessment of NAOMI’s counseling skills based on the MITI-coded transcripts has 2 components: global scores and behavior counts. The global scores aim to characterize the overall quality of patient-counselor interaction and include 4 dimensions (Cultivating Change Talk, Softening Sustain Talk, Partnership, and Empathy). Behavior counts are evaluated by tallying instances of specific counselor behaviors, which can be grouped into 5 broad categories: questions, reflections, MI adherent behavior, MI nonadherent behavior, and neutral behaviors. The global scores and behavior counts will then be used to assess the level of NAOMI’s counseling skills according to the MITI manual.

#### Qualitative Analysis

Due to the small sample size, only qualitative analysis of changes in the measures of perceptions of AI agents and counselors (administered in the Pre- and Post-Interaction Questionnaires) and motivational precursors (administered in Pre-, Post-Interaction, and Follow-Up Questionnaires) will be performed.

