### Goals of This Study

The main objectives of this study are 2-fold. The primary objective is to explore the feasibility of conducting unscripted weight loss MI with a fully automated LLM-based AI counselor by developing Neural Agent for Obesity Motivational Interviewing (NAOMI), a Web app for MI-style weight loss counseling. The secondary objectives are to test the acceptability and usability of NAOMI’s counseling and examine its ability to shift motivational precursors in a sample of overweight and obese patients recruited from primary health clinics.

Because this is a feasibility study involving a single interaction with NAOMI, it is not expected that participants will experience anthropometric changes. Participants will be advised to continue their current weight loss interventions (if any) and those who wish to engage in a weight loss intervention will be encouraged to contact their primary care provider for a referral to a weight loss treatment.

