### Study Hypotheses

This study will explore the following hypotheses: (1) NAOMI will achieve at least intermediate MI fidelity based on Motivational Interviewing Treatment Integrity (MITI) coding scheme [111] (see the Statistical Analysis subsection of the Methods section for more details); (2) At least 80% of the last cohort of study participants will find NAOMI acceptable and usable; specifically, they will like using NAOMI, be comfortable discussing their weight with it, find their interaction with it pleasant, its guidance helpful, and want to use it again (see the Measures subsection of the Methods section for more details); (3) Interaction with NAOMI will result in positive shifts in all motivational precursors (see the Qualitative Analysis subsection of the Methods section for more details).

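### Hypothesis 3 predicts positive shifts on three paired 1-10 rulers, but the plan limits their analysis to a qualitative one and defines neither a summary measure, a contrast nor a positive shift

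*Protocol article*

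**What the plan says.** Study Hypotheses states as its third hypothesis: "Interaction with NAOMI will result in positive shifts in all motivational precursors (see the Qualitative Analysis subsection of the Methods section for more details". All three hypotheses are introduced with "This study will explore the following hypotheses", and Goals of This Study lists this aim among the secondary objectives: "examine its ability to shift motivational precursors in a sample of overweight and obese patients recruited from primary health clinics".

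The precursors are numeric. The Pre-Interaction Questionnaire asks participants to "rate their confidence, importance, and readiness to change their weight-related lifestyle behaviors using a ruler ranging from 1 to 10". The same three rulers return in the Post-Interaction and Follow-Up Questionnaires, so each completer gives three scores per ruler.

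The Qualitative Analysis subsection, to which Hypothesis 3 refers, is one sentence. It opens "Due to the small sample size, only qualitative analysis of changes in the measures of perceptions of AI agents and counselors" and goes on to include the motivational precursors at all three time points. The Abstract repeats the restriction.

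**The concern.** A directional prediction about paired numeric scores needs at least a measure of change, a stated contrast and a meaning for a positive shift. The cited subsection supplies none of these, and no other analysis subsection fills the gap. Statistical Analysis covers only the MITI coding, and Thematic Analysis covers only the transcribed interviews.

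This is not a detail left to an unseen analysis plan. The article restricts the analysis explicitly and gives a reason, so a later plan that added paired estimates would depart from it.

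At stake is how Hypothesis 3 will be read. Without a definition fixed beforehand, the contrast, cohort and summary can be chosen after the scores are seen. The Conclusions also announce a randomized trial of efficacy on these same precursors. The size and spread of the change would be useful for designing it, and the present text does not commit to reporting either.

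**Working it through.** **1. The plan's own sample size.** Inclusion Criteria and Target Sample Size gives 50 recruited for 40 completers, 10 in each of 4 cycles.
- Implied attrition: 1 - 40/50 = 20%.
- Check: 40/(1 - 0.20) = 50, and 50/4 = 12.5, which matches the stated 12-13 per cycle.

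The figures reproduce. The article states no power, alpha or effect size for Hypothesis 3.

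**2. The three hypotheses side by side.**

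| Hypothesis | Criterion in the article | Method in the article |
|---|---|---|
| 1, MI fidelity | At least an intermediate level on MITI | MITI coding, under Statistical Analysis |
| 2, acceptability and usability | At least 80% of the last cohort | Likert questionnaires |
| 3, motivational precursors | None beyond positive shifts in all | Qualitative only |

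Only the third has no criterion.

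**3. Does a small sample rule out estimation?** For a mean paired change, the 95% interval half-width in units of the SD of change is t(0.975, n-1)/√n.
- n = 10 (completers per version): 2.262/√10 = 0.72 SD.
- n = 40 (all completers): 2.023/√40 = 0.32 SD.
- n = 40 adjusted for four stages (36 degrees of freedom): 0.32 SD.

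The documents give no SD of change. Assuming 1 to 3 ruler points, the half-width is 0.72 to 2.15 points at n = 10 and 0.32 to 0.96 points at n = 40. These intervals are wide per version and moderate when pooled. Both can be reported.

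The half-width at n = 50 is 0.28 SD. It could apply only to pre-to-post change if everyone recruited attends the visit. The one-week change is planned on 40.

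**4. Would a formal test be reasonable?** With a paired t-test, 80% power and two-sided 5%, the detectable change is about 1.0 SD at n = 10 and 0.45 SD at n = 40, for one ruler. The hypothesis asks for all three. At a true change of 0.454 SD on each ruler and n = 40, the chance that all three intervals lie above zero is:
- independent rulers: 0.80³ = 0.51;
- correlation 0.5: about 0.61 (simulated);
- correlation 0.7: about 0.66 (simulated).

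The correlations are assumptions. A joint test is therefore underpowered even when pooled, and this supports estimation over testing.

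**5. Is the direction of the means enough?** The article states no such rule, so this is only an illustration. With no true change, all three mean changes are positive by chance with probability 0.125 (independent rulers), 0.25 (correlation 0.5) or 0.31 (correlation 0.7). Direction has to be read together with an interval.

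**The case against.** The strongest reply is that this is a feasibility study with exploratory hypotheses, that precursors are secondary, and that efficacy is deferred to a randomized trial. The primary objective rests on MITI coding and is untouched. All of this stands and sets the severity.

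Qualitative may also be meant loosely, as descriptive inspection of score changes without testing. The sentence does speak of changes in measures, and interviews are handled separately. That reading is plausible. A reader might infer from the text that no result could refute Hypothesis 3, but under this reading a flat or falling ruler would count against it. A reader might likewise infer that means and SDs will never be produced. The scores will exist, and the article merely does not commit to summarizing them. Even so, the loose reading supplies no summary, contrast or definition of a positive shift.

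It can also be said that 40 pairs combine different interventions. This is correct. Under System Versions and Training, stages 1 and 2 use different approaches and later stages refine the better one, and the Limitations concede cohort effects. The number per version is about 10, so the authors' caution about testing is sound and a pooled estimate can only be secondary.

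Finally, the plan states "Participants will be advised to continue their current weight loss interventions (if any", and a reader might blame those concurrent interventions for a pre-to-post change. A session of at most one hour makes that implausible. They bear on the one-week score. The causal wording of "Interaction with NAOMI will result in positive shifts in all motivational precursors" remains unsupported for a simpler reason: there is no control group.

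**Conclusion.** The point holds at moderate severity. Hypothesis 3 is directional and rests on paired numeric scores, while the subsection it cites allows only a qualitative analysis and gives no way to summarize or judge the change. The stated reason justifies forgoing a formal test. It does not justify forgoing estimates, whose 95% half-widths would be about 0.72 SD per version and 0.32 SD pooled.

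The half-widths rest on the planned 10 and 40 completers and on a t-interval for the mean change. Their conversion to ruler points depends on the assumed SD of 1 to 3. The documents do not support the stronger conclusions that the hypothesis is untestable in principle or that a powered test on 40 to 50 pairs should have been planned.

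**What to change.** Replace the sentence under Qualitative Analysis, and the matching sentence in the Abstract, with a descriptive quantitative analysis:

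- For each ruler, report the mean paired change, its SD and 95% interval, and the numbers improved, same and worse.
- Make pre-to-post the main contrast and pre-to-one-week supportive.
- Report by NAOMI version with the final cohort shown separately. Give a pooled estimate adjusted for stage as secondary, because the versions differ.
- Treat the 5-point perception items that are asked both before and after the session in the same way (pre-to-post only).
- Define a positive shift as a mean pre-to-post change above zero, read with its interval. A lower limit above zero is clear evidence. Anything else is inconclusive or contrary. State that this is not a powered test.
- Reword Hypothesis 3 as an observed pre-post change instead of a result of the interaction.

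A qualitative description can stay as a supplement. The cost is one paragraph and a few hours of analysis, with no new data or participants. The downside is that the wide per-version intervals become visible.

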#### Thematic Analysis

Framework matrix analysis [125], an efficient, systematic approach to thematic analysis that begins with the construction of a matrix based on content areas derived from the interview guide, will be used to analyze transcribed qualitative interviews. Two coders will independently code the interviews by “charting” a summary of feedback into the matrix. Coders will meet to review and compare their matrices, resolve discrepancies, and develop a final coded-to-consensus matrix. Coders then identify emergent themes to summarize users’ experience with NAOMI and suggestions for intervention modification.

### Ethical Considerations

This research protocol was reviewed and approved by the institutional review board of Wayne State University (protocol IRB-23-01-5404), as amended, on May 25, 2024. After completing the study visit, the participants will be compensated with a US $75 Amazon gift card. A US $15 Amazon gift card will be provided to the participants after completing the Follow-Up Questionnaire. The data set for fine-tuning the LLM underlying NAOMI is fully deidentified. Transcripts of participants’ interactions with NAOMI will be modified by the study staff after the interaction to remove any identifying information. Audio and video data collected during qualitative interviews will be transcribed and deidentified. After transcription has been completed and the integrity of the data confirmed, the audio and video files will be destroyed. All survey data will be collected using a unique research identification number, which will also be used as a link to the participant’s survey data and to label the data derived from the participant’s interaction with NAOMI. The linkage between the research identification number and the participant’s identity will be maintained in a password-protected file stored on a secure server.

## Results

The first version of NAOMI has been developed. The investigative team also developed a website for the study visit, which will allow only study participants to access NAOMI, automatically guide the participants through the steps of the study visit detailed in Textbox 1, keep track of their progress, and allow them to complete the study visit only once. Participant recruitment will commence in September 2024. Data collection activities are expected to conclude in May 2025.

## Discussion

### Study Hypotheses

This study explores the hypotheses that NAOMI, an LLM-based AI counselor, can conduct unscripted weight loss MI sessions achieving: (1) at least intermediate MI fidelity; (2) 80% user satisfaction, and (3) positively shifting motivational precursors. LLM-based counselors have the potential to address the following limitations of scripted counselors.

First, LLMs can generate fluid, diverse, and knowledgeable AI agent responses that take into account previous interactions in a conversational session. Diversity (mixing informational statements, questions, reflections, and affirmations) and contextual relevance of counselor responses are integral parts of MI. Receiving short, generic, or repetitive replies from scripted and retrieval-based conversational agents for mental health care in response to deeply personal questions has been identified as one of the primary reasons for patient dissatisfaction in prior qualitative studies [87].

Second, LLMs possess human-level capabilities for generating fluent and coherent content. They recognize fine nuances of language and can be taught the concepts of style and tone. They can also pay close attention to patient language and communicate emotions and empathy. Understanding and paying attention to the nuances of patient language is necessary to generate engaging and contextually relevant responses.

Third, due to the open and loosely structured nature of MI counseling sessions, it is infeasible to capture all possible session contexts and scenarios with a finite set of rules, patterns, scripts, or dialog states. As part of this study, we will explore the feasibility of training LLMs to conduct MI counseling sessions by using context-appropriate provider communication skills to elicit target patient language and respond to client resistance.

